This protocol is reported following Standard Protocol Items: Recommendations for Interventional Trials guidelines.^22^ The overall aim of this randomised controlled trial is to evaluate the comparative effectiveness and acceptability of CBT-T for non-underweight clients with EDs aged 15 years and above to CBT-TA. To achieve this, participants will be randomised to either receive CBT-T or CBT-TA. Our first specific aim is to examine superiority of CBT-TA (in clinically determined gradual responders) against a CBT-T control group. The secondary research aim is to examine superiority of CBT-TA (in clinically determined rapid responders) against a CBT-T control group. We also will address an exploratory aim, namely, whether any differences exist between CBT-TA (passive augmentation) in clinically determined rapid responders vs CBT-TA (active augmentation) clinically determined gradual responders.

First, we hypothesise that gradual responders in CBT-TA will have significantly lower ED psychopathology compared with gradual responders in CBT-T at end of treatment and that these gains will be maintained at the 3-month and 6-month follow-up. We also hypothesise that remission will be higher in the former than latter group. Second, we hypothesise the same advantages for the rapid responder group in CBT-TA over rapid responders in CBT-T. We will also explore (1) change in health service utilisation including primary, secondary and tertiary care, (2) engagement and completion data between the two conditions to establish the relative acceptability of the interventions, and (3) client’s experiences of therapy in the form of qualitative feedback.

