### Other measures

Other measures include demographics, functions of self-harm, healthcare use, and feedback about the service (aspects least and most liked), and acceptability as indicated by the number of sessions completed and premature cessation of therapy (drop-out). Demographic information will include ED diagnosis, age, duration of the ED, cultural identity, previous mental health treatment, gender, socioeconomic status, and one item assessing importance of change and ability to change. The functions of self-harm will be assessed only at baseline to inform treatment, using Section II of the ISAS,^43^ consisting of 39 items scored on a 3-point scale: not relevant, somewhat relevant and very relevant. There are 13 function subscales: affect regulation, interpersonal boundaries, self-punishment, self-care, anti-dissociation/feeling-generation, anti-suicide, sensation-seeking, peer-bonding, interpersonal influence, toughness, marking distress, revenge and autonomy. Healthcare use will assess the type and frequency of healthcare use over the previous 3-month period. The BA-SSI completion item will ask participants to estimate how much of the SSI they completed, on a sliding scale from 0 to 100.

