### Sample size

A previous randomised controlled trial completed at FUSED showed that less motivated clients receiving CBT augmented with a small amount of motivational content had significantly better outcomes at 1-month follow-up than those who did not receive this content.^25^ At 3-month follow-up, a between-group effect size (Cohen’s d) benefit persisted of 0.37 (−0.20 to 0.93). Based on a power of 0.80, alpha of 0.05, assuming a correlation of 0.50 between baseline and post-training assessments, a small between-group effect size d=0.35 and 10% attrition between each of the 5 waves of data collection (40% attrition in total), we will be required to randomise 162 participants to CBT-TA and 68 participants to CBT-T (n=230).^44^ Over previous trials, around 50 clients have completed treatment at FUSED annually. To ensure we can randomise 230 clients over 4 years, we will open referrals to people with binge eating disorder (previously not eligible for a service), add four registered clinical psychologists who will have an ongoing client load of 2–5 people to the usual staffing of clinical psychology postgraduate trainees, and advertise the service.

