Analyses will be undertaken with a treatment-policy approach (ie, intention-to-treat) and will include all participants in the group to which they were randomised, regardless of actual receipt or uptake of the intervention or withdrawal from the study (ICH E9 R1^45^). Mixed-model repeated measures analysis will be used for the continuously scaled primary outcome and secondary outcome variables. An unstructured residual variance-covariance matrix will accommodate within-participant dependency. The model will include factors of study condition (CBT-T, CBT-TA), occasion of measurement (baseline, 4, 10, 22 and 34 weeks post-randomisation) and their interaction as fixed effects, with a random intercept to account for variation between individual participants. The primary outcome will be assessed by a planned comparison of the difference between groups in change of the primary outcome variables over time. Given the assumption of MRMM that data are missing at random (MAR), multiple imputation will be used to replace missing observations. To examine robustness of the results and the MAR assumption, sensitivity analyses will be conducted using the tipping point and delta adjustment method. Additionally, we will run a number needed to treat analysis, based on the proportion of participants in each arm who meet the prespecified criteria for remission,^46^ (i) global EDE-Q score ≤2.77, (ii) BMI ≥18.5 and (iii) no ED behaviours in the previous 1 month period.

Analyses of secondary outcome variables will follow the same methods as the primary outcome except for the behavioural count variables, which will be analysed with generalised linear mixed modelling (GLMM). Separate GLMM models with a log link function and gamma distribution will be used to account for the right skewed health utilisation data.

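### A gamma mixed model is named for health-service use, a frequency that can be zero; the gamma likelihood is not defined at zero, so the treatment of non-users is left to software

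*Protocol article*

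**What the plan says.** The section on data collection, management and statistical analysis of the protocol article gives health-service use its own model: "Separate GLMM models with a log link function and gamma distribution will be used to account for the right skewed health utilisation data". Right skew is the only reason given.

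The variable is described under Other measures: "Healthcare use will assess the type and frequency of healthcare use over the previous 3-month period". The Introduction lists it among the matters to be explored: "change in health service utilisation including primary, secondary and tertiary care".

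The analysis section also states, for the analyses in general, that they "will include all participants in the group to which they were randomised", whatever intervention was received and whether or not the participant withdrew.

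The article does not mention zero use, a two-part or hurdle model, an added constant, or conversion of use into cost. In Table 1 the service-use row carries two marks, against six for the eating disorder questionnaire. The column alignment is lost in the text available, so the two occasions cannot be identified.

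**The concern.** Right skew alone would make a log-link gamma model a sensible choice for a strictly positive amount, such as the cost of care among people who used some. A frequency of contacts over three months is a different kind of variable: it is a non-negative count, and zero is an ordinary value. The gamma distribution has no place for zero, so the named model does not fit the named variable.

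At stake is what happens to participants who used no service of a given type. If they are removed, the comparison is of intensity among users only, a group formed after randomisation. A treatment that changed whether people use a service, but not how often users use it, would show no effect in that comparison. The analysis would also no longer include everyone randomised, as the plan says it will.

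**Working it through.** There is no stated figure to reproduce. The point concerns the range of values that a distribution allows. Three checks were made.

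**1. Gamma density at zero.** With shape a and scale s, the log-density is

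log f(y) = (a − 1) log y − y/s − a log s − log Γ(a), for y > 0.

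As y falls to 0, the first term goes to +∞ if a < 1 and to −∞ if a > 1. Evaluated at y = 0, the log-density is +∞ for a = 0.5 and −∞ for a = 2. It is finite only in the boundary case a = 1. A single zero therefore makes the likelihood unusable for estimating the shape.

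**2. How common zeros might be.** The article gives no use rates, so the three-month means m below are assumptions. Poisson: P(0) = exp(−m). Negative binomial with size 1: P(0) = 1/(1 + m).

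| Assumed mean contacts | Zeros, Poisson | Zeros, negative binomial |
|---|---|---|
| 0.5 | 61% | 67% |
| 1 | 37% | 50% |
| 2 | 14% | 33% |
| 4 | 2% | 20% |

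For a rarely used type of care the share is large. For a total over all services it could be small.

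**3. What each treatment of zeros does.** Inputs from the Sample size section: 162 and 68 randomised, 40% attrition in total. That leaves 162 × 0.6 = 97.2 and 68 × 0.6 = 40.8, taken as 97 and 41. Assumptions: the arm affects only the probability of any use, and users in both arms average 3 contacts (1 plus a negative binomial with mean 2). The true ratio of mean use is then (p_TA × 3)/(p_T × 3) = p_TA/p_T, for example 0.30/0.60 = 0.50. The expected share kept after dropping zeros is (97 p_TA + 41 p_T)/138, for example (29.1 + 24.6)/138 = 39%. There was one time point and no random effect.

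| Any use, CBT-TA v CBT-T | True ratio | Kept if zeros dropped | Gamma, users only: ratio (rejects at 5%) | Ratio of means, everyone (robust Poisson rejects) | Any-use logistic rejects |
|---|---|---|---|---|---|
| 0.30 v 0.60 | 0.50 | 39% | 1.02 (8%) | 0.51 (62%) | 92% |
| 0.40 v 0.60 | 0.67 | 46% | 1.01 (6%) | 0.67 (33%) | 56% |
| 0.60 v 0.80 | 0.75 | 66% | 1.01 (5%) | 0.75 (29%) | 64% |
| 0.80 v 0.95 | 0.84 | 85% | 1.00 (7%) | 0.84 (19%) | 45% |

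These are 1000 runs per row. The users-only ratio is near 1 by construction, since users were given equal intensity in both arms.

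The third possibility is that software keeps the zeros. With a log link the gamma estimating equation, Σ x(y − μ)/μ = 0, can be solved with zeros present. Its solution for two arms is the pair of arm means. On six records (0, 2, 0 v 1, 3, 5) the fit returned coefficients −0.405 and 1.504, that is, means of 0.667 and 3, with an infinite log-likelihood. In the four scenarios above (500 runs each, robust standard errors) this gave ratios of 0.50, 0.68, 0.75 and 0.85 and rejected in 64%, 30%, 28% and 14% of runs.

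**The case against.** A reader might infer that non-users will be lost and that an arm effect on use will disappear. The article does not support that as a certainty. It follows only if the software drops zeros. If the program stops with an error, the analyst has to change the model before any result exists. If it solves the estimating equation with zeros included, the ratio of means is recovered, as shown above. Dropping non-users would also breach the plan's own rule on who is analysed. This objection stands, and it limits the claim to what may happen. It does not rescue the wording, because the result then rests on a software default that nobody chose. The quasi-likelihood check also had no random intercept, whereas the planned model is a mixed model.

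A reader might also take the simulated ratios as the size of the error in this trial. They are not. They follow from assumed use rates and from equal intensity among users.

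The frequency of zeros is inferred, not stated. Participants must consent to regular communication with their general practitioner, and many may be referred by a health professional, so zeros may be infrequent for primary care or for a total over services. The article does not say whether a count per type or a total is modelled. "Separate" models could mean one per type, or separate from the models for behavioural counts. This stands too. Even so, the stated aim extends to tertiary care, where zeros in an outpatient sample over three months are very likely.

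Finally, the unseen full plan may add a model for any use ahead of the gamma part. That is possible, but the article names a single gamma model for the utilisation data as a whole, and that statement is wrong as it stands.

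**Conclusion.** The concern holds in a limited form. The article names a gamma distribution for a variable that it defines as a frequency, and the gamma likelihood is not defined at zero. That part is mathematics and rests on no assumption. That zeros will occur is an inference: near certain for at least some types of care, less so for primary care or a total.

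The consequence depends on software. The model may stop, may drop non-users against the plan's own rule and hide an effect on any use, or may fit without a valid likelihood. No size of distortion can be given for this trial, because the share of zeros is not in the article. At assumed any-use rates from 0.30 to 0.95, dropping zeros would remove 15% to 61% of participants.

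Service use is exploratory. The primary outcome, the secondary outcomes and the sample size do not depend on it. The change is worth making because it is concrete and cheap now, whereas a change of model after the zeros are seen would be post hoc.

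**What to change.** In the analysis section, replace the gamma sentence with the following content:

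- Health-service use will be analysed with a negative binomial mixed model, with log link and a random participant intercept. State whether there is one model per type of care or one for the total.
- The fixed effects are condition, the occasions at which service use is actually collected, and their interaction. The five-occasion structure of the primary model should not be carried over, since Table 1 marks service use only twice.
- If zeros are excessive by a criterion set in advance, use a two-part (hurdle) model: any use, then the amount among users. Report the combined mean ratio over all participants, (p_TA × mean among CBT-TA users)/(p_T × mean among CBT-T users), so that everyone randomised still counts.
- Keep gamma only for strictly positive quantities.

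The cost is one or two sentences of analysis wording. Data collection, sample size and the primary and secondary analyses do not change, and standard mixed-model software should suffice.

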### Monitoring

The trial is overseen by the principal investigator ([name]) and the trial management group ([name], [name], [name], [name]). Day-to-day trial oversight will be provided by a PhD student ([name]) who will meet with the principal investigator on a weekly basis. All adverse events and serious adverse events and broader safety monitoring will be documented and reported to the trial management group by the principal investigator and reported in the primary outcomes paper. If there are concerns for participant safety, based on (but not limited to) deterioration of mental health, the trial management group may recommend pausing or terminating the trial. Adverse events will be reported to the ethics committee if appropriate. The trial is insured with AON policy # AUS21899001.

## Ethics and dissemination

Flinders University is the sponsor of this clinical trial and ethics approval was provided by the Social and Behavioural Research Ethics Committee at Flinders University (7992). The information and consent form for adults and minors can be found in onlinesupplements 1  2 respectively. The trial is covered by Flinders University general and liability insurance protections that will indemnify Flinders University staff and students. This trial was prospectively registered with the Australian New Zealand Clinical Trials Registry (20 December 2024; ACTRN12624001495516). The findings arising from the study protocol will be reported to participants and presented at scientific conferences and disseminated by publications submitted to peer-reviewed journals. The deidentified data set used and/or analyses will be available from the corresponding author’s Open Science Framework site.

## Data Availability

No data are available.
